## Abstract

**Background:**

Depression amongst adolescents is a costly societal problem. Little research documents the effectiveness of public mental health services in mapping this problem. Further, it is not clear whether usual care in such services can be improved via clinician training in a relevant evidence based intervention. One such intervention, found to be effective and easily learned amongst novice clinicians, is Interpersonal Psychotherapy (IPT). The study described in the current paper has two main objectives. First, it aims to investigate the impact on clinical care of implementing Interpersonal Psychotherapy for Adolescents for the treatment of adolescent depression within a rural mental health service compared with Treatment as Usual (TAU). The second objective is to record the process and challenges (i.e. feasibility, acceptability, sustainability) associated with implementing and evaluating an evidence-based intervention within a community service. This paper outlines the study rationale and design for this community based research trial.

**Methods/design:**

The study involves a cluster randomisation trial to be conducted within a Child and Adolescent Mental Health Service in rural Australia. All clinicians in the service will be invited to participate. Participating clinicians will be randomised via block design at each of four sites to (a) training and delivery of IPT, or (b) TAU. The primary measure of impact on care will be a clinically significant change in depressive symptomatology, with secondary outcomes involving treatment satisfaction and changes in other symptomatology. Participating adolescents with significant depressive symptomatology, aged 12 to 18 years, will complete assessment measures at Weeks 0, 12 and 24 of treatment. They will also complete a depression inventory once a month during that period. This study aims to recruit 60 adolescent participants and their parent/guardian/s. A power analysis is not indicated as an intra-class correlation coefficient will be calculated and used to inform sample size calculations for subsequent large-scale trials. Qualitative data regarding process implementation will be collected quarterly from focus groups with participating clinicians over 18 months, plus phone interviews with participating adolescents and parent/guardians at 12 weeks and 24 weeks of treatment. The focus group qualitative data will be analysed using a Fourth Generation Evaluation methodology that includes a constant comparative cyclic analysis method.

**Discussion:**

This study protocol will be informative for researchers and clinicians interested in considering, designing and/or conducting cluster randomised trials within community practice such as mental health services.

**Trial Registration:**

Australian Clinical Trials Registry ACTRNO12607000324415

## Background

The immediate and long-term individual, interpersonal and societal costs of depression are substantial [1]. Up to one in five people will have suffered the effects of major depression before the age of 18 years [2]. Despite limited research regarding depression amongst rural adolescents, we know that rural young men are at particularly high risk of suicide compared to their metropolitan peers [3]. Depression during adolescence typically complicates progression through the essential developmental tasks of that time leading to secondary difficulties [4,5]. To address such problems, effective and accessible treatment is needed. When detected, however, treatment provided for depression is often inconsistent with evidence-based treatment guidelines [6]. Whether or not such treatment discrepancy is problematic for adolescent outcomes remains unclear.

Questions remain regarding the most effective community treatment for adolescents with depression. Antidepressant medication continues to be associated with controversy regarding its efficacy and safety in use with adolescents [7]. Structured psychological interventions, particularly Cognitive Behaviour Therapy (CBT) and Interpersonal Psychotherapy (IPT), have demonstrated efficacy for the treatment of adolescent depression [8,9]. These psychotherapies are also used as treatments alongside medication, or in the maintenance of post depressive episodes.

Efficacy studies, requiring strict treatment and control conditions, typically exclude clients with complex clinical presentations. In reality, adolescents with depression frequently present with comorbid mental or substance-use disorders [10]. Effectiveness trials are needed to investigate the feasibility and value of implementing structured psychological interventions in community practice.

The available evidence suggests IPT is an efficacious treatment for depression [11] which can be easily learned by Australian mental health professionals [12] and other novice therapists [13,14]. IPT is based on the formulation that relationships are inherently inter-related with emotional wellbeing. The therapy aims to decrease depressive symptomatology and improve the relational functioning of clients. The treatment focuses on a key interpersonal problem area identified for the individual (e.g. grief, interpersonal role disputes, interpersonal role transitions). IPT is manual-based and time-limited and can be administered effectively with or without medication [15].

From a systematic review of IPT efficacy in the treatment of depressive spectrum disorders between 1974 and 2002, a meta-analysis of 13 studies found IPT superior in efficacy to placebo for mean improvement in depressive symptoms (weighted mean difference [WMD] = -3.57; 95% confidence interval [CI] -5.98, -1.16) and lower short-term drop out rate (relative risk [RR] = 0.59; 95% CI 0.36, 0.99). IPT was similar in efficacy to medication and did not increase when combined with medication. IPT performed significantly better than CBT for mean difference improvement (WMD = -2.16; 95% CI -4.16, -0.15) though not for total remission [16].

Interpersonal Psychotherapy for Adolescents (IPT-A) has evolved from the adult version (IPT), making adaptations for the developmental issues of adolescents. Amongst adolescents with depression, IPT-A has been demonstrated to be superior to Treatment as Usual (TAU) in an effectiveness study of five school-based mental health clinics in New York [17]. In a trial with Puerto Rican adolescents, remission of depressive symptoms was achieved by 82% of adolescents receiving IPT-A and 59% receiving CBT. Compared to the waiting list control, those in an IPT-A group showed increased self-esteem and social adaptation [18]. IPT-A has also demonstrated effectiveness in the treatment of moderate to severe depression in adolescents by well-supervised novice IPT-A therapists [13].

IPT appears a promising intervention to trial for the treatment of adolescents with depression attending a rural Child and Adolescent Mental Health Services (CAMHS). CAMHS aims to treat adolescents presenting with severe, usually comorbid, mental health difficulties. In rural areas this is complicated by limited availability of mental health specialists. IPT appears particularly valuable in this context given its appeal to clinicians and easy delivery by a broad range of mental health professionals. The TAU of adolescent depression in CAMHS is, on contrast, poorly defined and of unknown quality or effectiveness.

The current project explores the impact of implementing IPT in a rural CAMHS and the feasibility of comparing IPT and TAU in practice. Given that implementation and evaluation of interventions in health services is typically complex, a qualitative process evaluation will be incorporated to explore the contextual factors associated with the implementation [19].

The objectives of the clinical research are:

1. to investigate the impact on clinical care of implementing IPT for the treatment of adolescent depression within a rural CAMHS compared with TAU.

2. to evaluate the issues associated with implementing a cluster randomised clinical trial in CAMHS (i.e. feasibility, acceptability, sustainability).

## Methods/Design

### Sample

The research is being conducted within the LRH CAMHS in rural Victoria, Australia. The service provides care for children and adolescents across 40,000 square kilometres with a population of 236,000. All clinicians, employed full- or part-time within the LRH CAMHS, other than the principle investigator, are invited to participate. At the time of writing this includes 18 clinicians based at four sites. The clinicians comprise psychologists, social workers, occupational therapists, mental health nurses and a psychiatry registrar. The trial aims to include a minimum of 60 adolescent clients of LRH CAMHS, aged 12 to 18 years inclusive, to be recruited over 12 months. The sample size was determined on the basis of logistic feasibility and resource constraints. In addition, given the lack of information about the likely size of the intra-class correlation coefficient (ICC), one intention of this study is to estimate this statistic to assist in sample size calculation for a larger subsequent effectiveness trial [20].

### Inclusion/Exclusion criteria

Adolescents are eligible to participate if (a) they meet the clinical cut-off for significant depressive symptomatology in the Reynold's Adolescent Depression Scale – 2^nd ^Edition (RADS-2) (T ≥ 61) [21], or (b) receive a DSM-IV-TR [22] or ICD-10 [23] diagnosis of a depressive disorder (i.e. Major Depressive Disorder (MDD), Dysthymic Disorder, Depressive Disorder NOS, or Adjustment Disorder with Depressed Mood) as affirmed by the team psychiatrist, and (c) have a Children's Global Assessment Scale (CGAS) [22] of 65 or lower. Clients will need parental/guardian consent to participate and the agreement of the CAMHS consultant psychiatrist. Adolescents will not be included if they are actively suicidal, have a life-threatening condition, psychosis or schizophrenia. Parents/guardians are eligible to participate if their adolescent child is participating and they have no exclusion criteria.

### Design

Approval for the research has been given by the Latrobe Regional Hospital (LRH) Human Research Ethics Committee (HREC) and the Monash University Standing Committee on Ethics in Research Involving Humans (SCERH).

#### Randomisation

A cluster randomisation design was chosen over simple client randomisation to overcome the obstacles of randomizing adolescents to treatment streams (i.e. to specific clinicians). Randomisation of adolescents could not be assured given limitations on the availability of specific clinicians at any given time and site.

The clinical assignment allocation process involves block randomisation of participating clinicians within each of the four sites to either IPT training or TAU. Allocation of clients to clinicians continues as per usual practice of availability. Randomisation was conducted centrally.

#### Treatments

The IPT stream comprises 12 weekly manual-based sessions with the adolescent. The TAU stream comprises usual care for the client. This may involve, for example, individual counseling, family work, liaison with schools and other professions, psychopharmacology, etc. In both streams the clinician will record monthly the treatment strategies used, the frequency of sessions, any additions or changes in medication, and any critical incidents which have occurred.

#### Concurrent process evaluation

Implementation issues will be investigated qualitatively using quarterly focus groups with clinicians and through individual telephone interviews with adolescent participants and their parent/guardians after receiving 12 weeks and 24 weeks of treatment. The telephone interviews with participating adolescents and parent/guardians will follow a semi-structured schedule to guide the interview. The questions will explore the participant's views on the treatment provided. Example questions include, 'How effective do you feel the treatment has been that you have received at CAMHS?', 'What have been the most helpful components of the treatment?' and 'What changes would you recommend in the treatment you have received at CAMHS?' The interview will take approximately 20 minutes.

A preliminary action research project was conducted with the LRH CAMHS clinicians to encourage clinician input and engagement in the design of the project. This comprised focus groups conducted with clinicians between three and five occasions during 2006. This process helped to shape the research to the clinical environment, and the clinical environment to research involvement.

### Main outcome measures

Monitoring and outcome assessment will use reliable and valid measures applied in similar research. These include adolescent self-report, parent-report and clinician ratings:

#### 1. Clinician-rated diagnostic status and clinical severity

a. Health of the National Outcome Scales (HoNOSCA) [24]. This is a global measure of child and adolescent mental health status. It is a standard CAMHS outcome measure used to rate changes in CAMHS client behaviour, impairment, symptoms, and social functioning.

b. CGAS [22]. The CGAS, presented in the DSM-IV-TR, is a clinician-rating scale (1 through 100) used rate the general functioning of children and adolescents.

c. Treatment Recording Sheet (TRS). This clinician-report record was adapted with CAMHS clinician input from the Hawaii Child and Adolescent Mental Health Division (CAMHD) Intervention Strategies Codesheet and Codebook [25]. It is a monthly record of specific intervention strategies used with an adolescent. It also records any critical incidents or medication changes occurring for the adolescent during that month. Its development is discussed elsewhere.

#### 2. Self-report

a. RADS-2 [21]. This adolescent-report measure takes 5 to 10 minutes for an adolescent to complete and has a Grade 3 reading level. It is a screening measure for adolescent depression, providing a clinical cut-off for ratings of mild, moderate and severe depressive symptomatology as well as six critical items for clinical consideration. It shows good reliability and validity.

b. Strengths and Difficulties Questionnaire (SDQ-S) [26]. The SDQ-S is a standard outcome measure administered in CAMHS. It is a brief behavioural screening questionnaire for children and adolescents. It includes items related to emotional, conduct, and hyperactivity/inattention symptoms, peer problems and prosocial behaviour.

c. Multidimensional Adolescent Satisfaction Scale (MASS) [27]. The MASS is a 21-item scale measuring adolescents satisfaction with various dimensions of mental health service treatment. It has good reliability and demonstrated convergent, discriminate, and predictive validity. Its subscales include counselor qualities (perceived competence of the clinician and quality of the relationship), meeting needs (perceived adequacy of quantity and type of service received), effectiveness (perceived benefit of service), and counselor conflict (experience of negative interactions with counselor).

d. Client Satisfaction Questionnaire (CSQ-8) [28]. The 8-item CSQ-8 consists assesses overall level of satisfaction with the treatment received.

#### 3. Parent-report

a. Strengths and Difficulties Questionnaire (SDQ-P) [26]. The SDQ-P is the parent-version of the SDQ, as described above

b. Short Mood and Feelings Questionnaire – Parent Version (SMFQ-P) [29]. The SMFQ-P is a 5 minute 13-item uni-dimensional parent-report measure of their child/adolescent's depressive symptomatology. It shows good internal reliability and discriminated between psychiatrically referred and non-referred children.

c. Client Satisfaction Questionnaire (CSQ-8) [28]. This measure is described above.

#### 4. Other

Demographic details of clients. Age, gender, previous mental health treatment, medication, parental occupation, family members in home, and ethnicity were recorded.

#### 5. Process evaluation

Evaluation questionnaires will be administered to all clinicians regarding use of the TRS at onset of research involvement and after 18 months. Evaluation of the IPT training will be conducted with IPT-trained clinicians immediately pre- and post-training and at 18 months follow-up. Focus groups conducted quarterly with clinicians will explore (a) contextual information regarding the research implementation (to assist interpretation of the quantitative trial results [19]), and (b) the feasibility, acceptability and sustainability of conducting the clinical research in CAMHS. Individual telephone interviews with adolescent participants and their parent/guardians will explore their satisfaction with treatment. Responses will be audio-tape recorded and transcribed.

## Analysis of results

### Quantitative analysis

Analysis will adopt an intention-to-treat design. The primary quantitative outcome measure will be change in depressive symptomatology. This will be evaluated as (a) the proportion of clients per treatment group with remission of depressive symptoms, defined as RADS-2 score below the clinical cut-off; (b) the proportion of clients per treatment group with clinical improvement of depressive symptoms, defined as having a 50% or higher reduction of depressive symptoms; (c) the difference in mean depressive symptoms post-treatment. The secondary quantitative outcome measure will be group differences in adolescent and parent/guardian satisfaction with treatment at 12 weeks and 24 weeks after start of treatment. Treatment acceptability will also be measured by proportion of clients per treatment group who do not complete treatment [16].

The quantitative analyses will compare group differences (i.e. remission, clinical improvement, mean difference, and non-completion) between the IPT and TAU groups. These analyses will allow estimation of the effect size of IPT on these outcomes. Comparison will be made between baseline and outcomes at 12 weeks and 24 weeks from start of treatment. Our main aim is one of estimation rather than hypothesis testing. Thus, effect sizes with 95% confidence intervals will be calculated in favour of significance testing in order to provide information for subsequent trials.

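### Remission has no baseline condition, so a client who enters by diagnosis with RADS-2 already below the cut-off counts as remitted at week 0

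*Protocol article*

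**What the plan says.** Under Inclusion/Exclusion criteria, an adolescent qualifies by reaching the RADS-2 clinical cut-off of T ≥ 61, "or (b) receive a DSM-IV-TR [22] or ICD-10 [23] diagnosis of a depressive disorder". The listed diagnoses include Dysthymic Disorder, Depressive Disorder NOS and Adjustment Disorder with Depressed Mood. A further condition is to "have a Children's Global Assessment Scale (CGAS) [22] of 65 or lower".

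Under Quantitative analysis, the primary outcome is introduced as change in depressive symptoms and is then expressed in three ways. The first is "the proportion of clients per treatment group with remission of depressive symptoms, defined as RADS-2 score below the clinical cut-off". The second is the proportion with at least a 50% reduction, and the third is the difference in mean symptoms after treatment. The section also states: "Analysis will adopt an intention-to-treat design". It sets no baseline condition for remission and no separate rule for clients who enter by diagnosis.

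**The concern.** The article fixes both the entry rule and the outcome rule, and the two do not fit together. The diagnostic route widens entry beyond the RADS-2 route only by admitting clients below the cut-off. Those clients satisfy the remission definition before treatment starts. A client who worsens but stays below 61 would also be counted as remitted.

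Two consequences follow if such clients are enrolled. Where both arms have the same share of them, the remission difference is diluted. Where the shares differ, a difference can appear without any treatment effect. Randomisation of clients does not guard against the second: only clinicians are randomised, clients reach them by availability (Randomisation), and the Discussion concedes that this is likely to bias the allocation of cases. The study exists to supply effect estimates for a later trial, so a distorted remission estimate would carry into that planning.

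**Working it through.** **Step 1: set the two rules side by side.**
- Entry requires RADS-2 T ≥ 61 or a diagnosis, and CGAS of 65 or lower. However the sequence (a), (b), (c) is grouped, diagnosis plus CGAS is enough. CGAS rates general functioning and sets no floor on RADS-2.
- Remission requires only a RADS-2 score below the clinical cut-off. The only numerical cut-off in the article is T ≥ 61, and I take it to be the one meant.
- A client with a qualifying diagnosis, CGAS of 65 or lower and T < 61 is therefore both eligible and, at week 0, remitted.

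**Step 2: is there a figure to reproduce?** No. The article gives no remission rates and no share entering by diagnosis alone. On sample size it says: "The sample size was determined on the basis of logistic feasibility and resource constraints". All rates below are assumptions.

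**Step 3: formula.** For one arm, let q be the share below the cut-off at week 0, p the remission rate among those at or above it, and s the probability that a low entrant is below the cut-off at follow-up. Then

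observed remission = (1 − q) × p + q × s.

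**Step 4: equal shares in both arms.** If q and s are the same in both arms, the s terms cancel and

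observed difference = (1 − q) × (p₁ − p₀).

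With p₁ = 40% and p₀ = 25%, the true difference is 15 points:

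| q | Observed difference (points) | Remitted at week 0, of 60 | Clients at T ≥ 61, of 60 |
|---|---|---|---|
| 10% | 0.9 × 15 = 13.5 | 6 | 54 |
| 20% | 0.8 × 15 = 12 | 12 | 48 |
| 30% | 0.7 × 15 = 10.5 | 18 | 42 |
| 40% | 0.6 × 15 = 9 | 24 | 36 |

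Check at q = 20% and s = 85%: 0.8 × 0.40 + 0.2 × 0.85 = 0.49, and 0.8 × 0.25 + 0.2 × 0.85 = 0.37, a difference of 12 points.

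**Step 5: unequal shares, no treatment effect.** With the same p and s in both arms,

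false difference = (q₁ − q₀) × (s − p).

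- p = 30%, s = 85%, q = 30% versus 10%: 0.7 × 0.30 + 0.3 × 0.85 = 0.465, and 0.9 × 0.30 + 0.1 × 0.85 = 0.355, a false difference of 11 points.
- p = 40%, same shares: 0.2 × (0.8 − 0.4) = 8 points at s = 80%, and 0.2 × (1.0 − 0.4) = 12 points at s = 100%.
- The sign reverses if the larger share falls in the other arm.

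**Step 6: with a baseline condition.** Restricting remission to clients at T ≥ 61 at week 0 sets q = 0. Nobody is remitted at entry, and the difference among those clients is the full p₁ − p₀.

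**The case against.** The mismatch in the text cannot be argued away, but several points limit its weight.

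- **Prevalence is unknown.** The abstract describes the sample as "Participating adolescents with significant depressive symptomatology, aged 12 to 18 years", and the entry criteria tie that kind of phrase to T ≥ 61. This suggests that low entrants are not the typical case, though it does not close the diagnostic route.
- **Context implies change.** Remission ordinarily presupposes symptoms at the start, and the plan compares baseline with 12 and 24 weeks. That comparison could expose the problem, but the printed definition still requires no transition.
- **The study is small and aims at estimation.** The plan says: "The trial aims to include a minimum of 60 adolescent clients of LRH CAMHS". No decision rule rests on remission, and the other two expressions of the primary outcome count nobody as a success at entry. With 49% versus 37% and an assumed 30 clients per arm, the 95% interval half-width is 1.96 × √(0.49 × 0.51/30 + 0.37 × 0.63/30) ≈ 25 points before clustering, against a dilution of 3 points. This lowers the severity but does not make the definition right.
- **Non-random allocation is a wider problem.** Arms that differ in baseline severity would also differ in remission among clients above the cut-off. A baseline condition removes only the part due to low entrants. This stands.

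A reader might infer that remission is certain to be inflated in both arms. The documents do not support that: they permit such entrants but do not say that any are expected.

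**Conclusion.** The point holds as a conflict between two rules that the article itself states, not as a detail left to an unseen plan. An analysis that followed the printed definition would count every client enrolled below T = 61 as remitted at week 0.

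The size is conditional. Equal shares reduce a true difference by the same proportion as the share, provided low entrants behave alike in both arms. Unequal shares of 30% and 10% would produce a false difference of about 8 to 12 points under the rates tried. None of these shares or rates comes from the documents.

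Severity is moderate. It would go too far to conclude that the primary result as a whole is invalid, because the 50% reduction and the mean difference do not share this fault.

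**What to change.** Define remission as moving from RADS-2 T ≥ 61 at week 0 to T < 61 at week 12 or week 24, with clients at T ≥ 61 at baseline as the denominator in both arms. Report the number of below-cut-off entrants by arm, and give the all-client proportion as a supplementary figure. All clients stay in the post-treatment mean comparison that the plan already contains.

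This takes a sentence or two in the analysis section and no new data, since the abstract already schedules assessments at weeks 0, 12 and 24. There are three costs:
- The remission proportion then describes only clients above the cut-off at entry. Under intention-to-treat this is a subgroup defined at baseline, and the text should say so.
- The denominator falls by the share of low entrants: from 60 to 54 at 10%, and to 36 at 40%. That loss is not slight if the share is large.
- Other bias from the non-random allocation of clients remains.

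### The primary outcome is three unranked definitions at two unranked weeks, and its mean comparison fixes neither the week nor the use of baseline

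*Protocol article*

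**What the plan says.** The Quantitative analysis section of the protocol article opens with one outcome: "The primary quantitative outcome measure will be change in depressive symptomatology". It then gives three ways of evaluating it and does not rank them:

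- (a) "remission of depressive symptoms, defined as RADS-2 score below the clinical cut-off";
- (b) "clinical improvement of depressive symptoms, defined as having a 50% or higher reduction of depressive symptoms";
- "c) the difference in mean depressive symptoms post-treatment".

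The next paragraph adds the times: "Comparison will be made between baseline and outcomes at 12 weeks and 24 weeks from start of treatment". Neither week is put first. The same paragraph says that the main aim is estimation, with effect sizes and 95% confidence intervals preferred to significance tests.

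The abstract describes the primary outcome differently: "The primary measure of impact on care will be a clinically significant change in depressive symptomatology". It also gives the schedule: adolescents "will complete assessment measures at Weeks 0, 12 and 24 of treatment", and "They will also complete a depression inventory once a month during that period".

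The Discussion acknowledges that cases are assigned by the team, without blinding or randomisation of clients, and that this will probably bias which clients go to which clinician.

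**The concern.** The heading promises change, but the third definition is worded as a comparison of means after treatment. A reader cannot tell whether it is a simple difference at follow-up, a difference in change scores, or a difference adjusted for baseline. These analyses differ in precision, and they respond differently to a baseline imbalance of the kind that the Discussion expects.

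Nor can a reader tell which week the comparison refers to, or which of the definitions leads. The effect sizes are meant to inform a larger trial. If all six results have equal standing, the most favourable one can be carried forward without departing from the written plan.

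**Working it through.** **1. The plan's own figure.** There is none to reproduce. The 60 clients rest on feasibility (Sample section), and no SD, effect size or power is given.

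**2. Number of primary results.** 3 definitions × 2 weeks = 6. No passage ranks the definitions or the weeks. The abstract's clinically significant change fits (a) and (b) better than (c), so it does not settle which leads.

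**3. What post-treatment can mean.** IPT is twelve weekly sessions (Treatments section), so it could end near week 12. TAU has no stated length. The abstract counts weeks 12 and 24 as weeks of treatment, and the Concurrent process evaluation section places interviews after 12 and after 24 weeks of treatment. Post-treatment therefore does not single out one of the two weeks for both arms.

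**4. Precision of the three readings of (c).** Inputs: 60 clients (Sample section), assumed split 30 and 30; equal SDs at baseline and follow-up; no clustering yet. The baseline-outcome correlation r is not in the documents and is assumed to be 0.3, 0.5 or 0.7. I read (c) on the RADS-2, the scale that (a) names.

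Half-width in SD units = 1.96 × √(2/30 × v), where v is the relative variance:
- follow-up means alone: v = 1
- change score: v = 2(1 − r)
- adjusted for baseline: v = 1 − r²

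| r | Follow-up only | Change score | Baseline-adjusted | Variance cut, adjusted against follow-up only |
|---|---|---|---|---|
| 0.3 | 0.51 | 0.60 | 0.48 | 9% |
| 0.5 | 0.51 | 0.51 | 0.44 | 25% |
| 0.7 | 0.51 | 0.39 | 0.36 | 49% |

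Example at r = 0.5: 1.96 × √(2/30 × 0.75) = 0.438. The adjusted estimate is the most precise in every row. The change score is worse than follow-up alone when r is below 0.5.

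**5. Clustering.** With 18 clinicians (Sample section) the mean cluster size is 60/18 = 3.3, and the design effect is 1 + (3.33 − 1) × ICC. For an assumed ICC of 0.01 to 0.20 this is 1.02 to 1.47. The follow-up-only half-width becomes 0.51 to 0.61 SD. The adjusted one at r = 0.5 becomes 0.44 to 0.53 SD, applying the same design effect. The relative gain is unchanged under that simplification.

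**6. Baseline imbalance.** Suppose the arms differ by D SD at baseline and follow-up depends linearly on baseline with slope r in SD units. The follow-up difference is then shifted by r × D, the change-score difference by r × D − D = −(1 − r) × D, and the baseline-adjusted difference by r × D − r × D = 0. This covers measured RADS-2 imbalance only. Selection on unmeasured features stays in all three.

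**The case against.** The best defence is that much of this is unstated rather than wrong. The outcome is headed change, definition (b) cannot be computed without baseline, and the section says that outcomes are compared with baseline. The exact model may stand in a full protocol or analysis plan that is not shown. For a feasibility-sized study aimed at estimation, reporting several candidate endpoints is reasonable. The correlations are assumptions, and entry partly on a RADS-2 cut-off may restrict the baseline range and lower them. At r = 0.3 the interval is only about 5% narrower (√0.91 = 0.954).

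Most of that stands, and it rules out four stronger readings that a reader might infer:

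- *That (c) is an unadjusted comparison which discards baseline.* The text never says so; it leaves the use of baseline unclear.
- *That no time is named.* Weeks 12 and 24 are both named. The gap is that (c) is tied to neither and neither is primary.
- *That monthly RADS-2 scores are thrown away.* The abstract does not name the monthly inventory, and the analysis section gives it no role. Silence is not exclusion, and the model could be specified elsewhere.
- *That six results inflate the false-positive rate.* A familywise rate describes tests, and this plan prefers intervals to tests.

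The defence does not reach what the article itself fixes: the list of primary definitions, the lack of any order, and the wording of (c). Defining the primary outcome is the article's own task, and here the result is ambiguous.

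**Conclusion.** The concern holds in a limited form. There are six unranked primary results, and one of the three definitions is worded as a post-treatment difference with no single week and no stated baseline adjustment, in a trial that expects biased assignment of cases. The consequence of the six results is room for selective emphasis.

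The gain from settling baseline use is a half-width of 0.48, 0.44 or 0.36 SD in place of 0.51 SD, at r = 0.3, 0.5 or 0.7. This assumes 30 per arm, equal SDs and no clustering. Clustering widens all of these intervals, and the use of 1.96 is somewhat optimistic with at most 18 clinicians. Adjustment also removes the measured part of any baseline imbalance, but it does not cure unmeasured selection. The abstract's different description of the primary measure is a minor mismatch that the same edit can resolve.

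**What to change.** In the Quantitative analysis section:

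1. Replace post-treatment in (c) with a named week, for example 12 weeks from start of treatment, with 24 weeks reported second.
2. State that (c) is the IPT minus TAU difference in RADS-2, adjusted for each client's baseline RADS-2, with an interval that respects clustering by clinician.
3. Name one definition at one week as the lead estimate, and report the other five results in full as supporting.
4. Make the abstract describe the same lead measure.

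Which definition leads is the investigators' choice; what matters is that it is fixed in advance. The form of the clustered model can be left to the analysis plan. It needs care there, because the Discussion notes that a site may have only one participating clinician, in which case arm does not vary within that site.

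The cost is wording. Baseline, week 12 and week 24 assessments are already scheduled, so no further data are needed. The one drawback is that five results lose equal primary standing.
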